### **Inclusion in the analysis**

Full analysis set (primary analysis, intention-to-treat): All patients included in the study will be analysed (contingent on availability of endpoints). Per-protocol set (secondary analysis): Only patients fully compliant with the protocol (especially regarding dosage) will be analysed. The full analysis set will be taken as safety analysis population as all patients will receive the study medication.

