colorectal cancer, has been shown to improve response rates in NSCLC when added to platinum-based chemotherapy (Gatzemeier, 2003). The two oral TKI gefitinib (IressaR) and erlotinib (TarcevaR) induce clinical responses in about 10% of relapsed NSCLC patients and stable disease in about 40% (Fukuoka et al., 2003; Kris et al., 2003; Shepherd et al., 2005). Chemotherapy-typical toxicity is avoided with acne-like skin lesions and diarrhoea representing the most prominent side effects. Recently, in a phase III multicenter trial of the National Cancer Institute of Canada a survival benefit was reported for relapsed NSCLC patients treated with erlotinib with a median survival time of 6.7 months (placebo: 4.7 months; (Shepherd et al., 2005). By comparison, despite impressive clinical responses in a subset of patients, no overall survival benefit in patients with relapsed NSCLC could be shown for gefitinib compared to placebo in a recently published randomized trial (Barge, 2004). Gefitinib had already received approval for the treatment of NSCLC patients after two chemotherapeutic treatment regimens in the USA, Japan, Australia and Switzerland due to the impressive clinical responses. But, until the final analysis of the data of the ISEL trial and further ongoing trials the administration of gefitinib is no more recommended (Barge, 2004). In the US and in the EU, erlotinib is approved for therapy of relapsed NSCLC after failure of at least one chemotherapy. Recently, first-line treatment of NSCLC patients in advanced stage (IIIB/IV) with erlotinib was evaluated in a phase II study and impressive clinical responses were reported. The non-progression rate was 55%. Best response was: 1 CR, 12 PR, 16 SD, 17 PD, 7 NE in this cohort (Giaccone, 2005). Furthermore, Jackman and colleagues performed a study in elderly patients with erlotinib monotherapy as a first line treatment. Efficacy was demonstrated with median 1 year survival rate of 46% and a median overall survival of 10.9 months comparable to results expected in the firstline treatment with combined platinum based chemotherapy (Jackman et al., 2007) (Schiller et al., 2002). In a German study using gefitinib monotherapy in the first line setting the progression free survival was described as 7 weeks (Reck et al., 2006). Further studies to test erlotinib in the line setting progression free survival are ongoing.

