## 2 AIM OF TRIAL

Based on the survival benefit demonstrated in patients with relapsed NSCLC (Shepherd et al., 2005) as well as on its favourable toxicity profile compared to chemotherapy the EGFR-TKI erlotinib represents an attractive candidate to be included also in protocols for the first line treatment of NSCLC. Accordingly, preliminary data from phase II trials show promising response rates for erlotinib treatment in the first line setting (Giaccone, 2005). In parallel, in the near future further targeted drugs will be available for NSCLC treatment. For instance, the addition of the anti-VEGF monoclonal antibody bevacizumab has recently shown to prolong survival when added to standard chemotherapy as first line treatment of NSCLC. Thus, in order to optimize the choice and the sequence of new drugs in NSCLC treatment, an early identification of patients with no clinical benefit, i.e. patients with progressive disease under treatment, is desirable. In the ERLOPET trial, we aim at establishing PET analysis as a tool for early identification of NSCLC patients with no clinical benefit from monotherapy with erlotinib as first line treatment. A pre-treatment computed tomography (CT) scan will be performed for evaluation of the patients' individual tumor burden. FDG- and FLT-PET scans will be performed between d -10 and d1 (but prior to therapy) for identification of pre-treatment PET status. Between d7 and d14, FDG- and FLT-PET scans will be performed for the early identification of erlotinib non responders. The imaging procedures will be performed at different days, i. e. one procedure per day. After six weeks of treatment, final response evaluation will be performed using CT, FDG- and FLT-PET scans. These results will be correlated to the mutational status of the EGFR - and the KRAS gene and the expression of EGFR in pretreatment samples.

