### **3.4 Termination of protocol treatment**

The patient can discontinue trial participation at his/her own wish at any time. Protocol treatment can be terminated based upon the decision of the treating physician, due to unacceptable toxicity, progression, serious intercurrent disease or pregnancy. In any case, following a formal or an actual termination, the patient's follow up should be documented.

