| grade 3 (stools $\geq$ 7)                                          | Interrupt                                            | interruption until resolution to grade $\leq$ 1, restart at reduced dose                                 |
| grade 4
(life threatening sequelae, e.g. haemodynamic collapse) | off study                                            |                                                                                                          |

Patients requiring a dose interruption for > 2 weeks due to not controlled adverse events of the Tarceva® medication will be taken off study.

In any case of a grade IV toxicity the patient will be withdrawn from the study. Any grade III toxicity will be reported to the principal investigator within 24 h after notice.

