#### **Endpoint**

##### **Primary endpoint**

Non-progression to therapy with erlotinib, FLT and FDG standard uptake values

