#### **Definitions and explanations**

Response criteria are according to the Response Evaluation Criteria in Solid Tumors (RECIST) (<http://www3.cancer.gov/bip/RECIST.htm>)

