### **Reporting of results**

- All patients included in the study must be assessed for response to treatment, even if there are major protocol treatment deviations or if they are ineligible. Each patient will be assigned one of the following categories: 1) complete response, 2) partial response, 3) stable disease, 4) progressive disease, 5) early death from malignant disease, 6) early death from toxicity, 7) early death because of other cause, or 9) unknown (not assessable, insufficient data).
- All of the patients who met the eligibility criteria should be included in the main analysis of the response rate. Patients in response categories 4-9 should be considered as failing to respond to treatment (disease progression). Thus, an incorrect treatment schedule or drug administration does not result in exclusion from the analysis of the response rate. Precise definitions for categories 4-9 will be protocol specific.
- All conclusions should be based on all eligible patients.
- Subanalyses may then be performed on the basis of a subset of patients, excluding those for whom major protocol deviations have been identified (e.g., early death due to other reasons, early discontinuation of treatment, major protocol violations, etc.). However, these subanalyses may not serve as the basis for drawing conclusions concerning treatment

efficacy, and the reasons for excluding patients from the analysis should be clearly reported.

- The 95% confidence intervals should be provided.

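### The primary set called intention-to-treat admits only patients with available endpoints, so early deaths, unimaged deterioration and withdrawals can drop out of the ROC analysis, and N = 40 has no reserve for such losses

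*Protocol*

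**What the plan says.** - **Analysis set.** Section 7.4 (Inclusion in the analysis) names a full analysis set, labels it intention-to-treat and limits it: "All patients included in the study will be analysed (contingent on availability of endpoints". The same paragraph makes this set the safety population, on the ground that all patients will receive the drug.
- **Endpoint.** Section 7.1 gives the primary endpoint as "Non-progression to therapy with erlotinib, FLT and FDG standard uptake values". Section 2 fixes the timing: "After six weeks of treatment, final response evaluation will be performed using CT, FDG- and FLT-PET scans". The imaging schedules (0.4, Table 1 in 5.5, and 5.9) place CT before treatment and in week 7 only.
- **Response rule.** Section 7.1 states: "Response criteria are according to the Response Evaluation Criteria in Solid Tumors (RECIST". Appendix 12.3 (Reporting of results) requires all included patients to be assessed. Its categories include early death from several causes and an unknown or not-assessable class. It adds: "Patients in response categories 4-9 should be considered as failing to respond to treatment (disease progression". It leaves the precise definitions of those categories to the protocol, and the protocol body gives none.
- **Leaving early.** Section 6.3: "In any case of a grade IV toxicity the patient will be withdrawn from the study". Section 3.4: "In any case, following a formal or an actual termination, the patient's follow up should be documented".
- **Size.** Section 7.3 needs 16 non-progressers and 24 progressers, 40 in total. Section 3.2 makes 40 the recruitment maximum.

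**The concern.** A set conditioned on having an endpoint is an available-case set, whatever its label. Here the availability of the outcome is linked to the outcome itself: a patient who dies of the cancer or declines quickly is less likely to reach the week-7 CT. Section 2 says the trial aims at early identification of patients with no clinical benefit, and some of those lost are probably such patients.

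Three things are at stake. The ROC sample may not represent the treated population. The 40 patients the calculation needs can be reached only if nobody is lost. And because the same set serves for safety, a patient who dies or is withdrawn early could, on a literal reading, be left out of the safety analysis.

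**Working it through.** **1. Who can be lost.** The endpoint has two parts, the response outcome and the SUVs.
- Progression documented before week 7: the outcome exists and the patient stays in.
- Death from disease, deterioration without imaging, or withdrawal before week 7: no scheduled CT provides an outcome. Under 7.4 read literally the patient is out; under Appendix 12.3 the patient counts as failure (progression).
- No PET between days 7 and 14: no SUV, so no outcome rule can bring the patient into the ROC.

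**2. The cited first-line cohort.** Section 1.2: "Best response was: 1 CR, 12 PR, 16 SD, 17 PD, 7 NE in this cohort".
- Total 1 + 12 + 16 + 17 + 7 = 53; non-progression 1 + 12 + 16 = 29.
- 29/53 = 54.7%, which matches the 55% the protocol reports. Dropping the 7 would give 29/46 = 63.0%. The quoted rate therefore keeps non-evaluable patients in the denominator, as the appendix does.
- Non-evaluable share: 7/53 = 13.2%, or about 5 of 40.

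**3. Reproducing N = 40.** Inputs from 7.3: AUC 0.75 against 0.5, two-sided 0.05 (the same critical value as the one-sided 2.5% in 7.2), power 80%, 24/16 = 1.5 progressers per non-progresser (R). The binormal variance is

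V = 0.0099 · exp(−A²/2) · [(5A² + 8) + (A² + 8)/R], with A = 1.414 · z(AUC).

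- Null: A = 0, V₀ = 0.0099 × 13.333 = 0.132.
- Alternative: A² = 0.910, V₁ = 0.0099 × 0.6346 × 18.49 = 0.116.
- Non-progressers: (1.96·√0.132 + 0.842·√0.116)² / 0.25² = 15.97, so 16; progressers 23.95, so 24; total 40.
- Half-width of the 95% interval: 1.96·√(0.116/16) = 0.167, stated as 0.17.

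The plan's figures reproduce.

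**4. Power when patients are lost from the 40.** With n₁ non-progressers analysed, power = Φ[(0.25 − 1.96·√(V₀/n₁)) / √(V₁/n₁)]. At 13.2% proportional loss n₁ = 13.9, and (0.25 − 0.191)/0.0915 = 0.644, giving 74.0%.

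| Loss (assumed) | Both groups in proportion | Progressers only |
|---|---|---|
| 0% | 80.1% | 80.1% |
| 10% | 75.6% | 77.0% |
| 13.2% | 74.0% | 75.8% |
| 15% | 73.1% | 75.0% |

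The half-width rises from 0.167 to between 0.172 and 0.181. All figures are for one tracer.

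**5. Direction of bias.** I simulated an equal-variance binormal model with a DeLong test, true AUC 0.75 and 5 of the 24 progressers missing. With none missing, simulated power is about 82%, slightly above the formula.
- Lost at random: AUC 0.75, power about 79%.
- The five progressers with values furthest from the non-progressers: AUC 0.69, power about 53%.
- The five with values closest to the non-progressers: AUC 0.85, power about 97%.

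The last two are deliberate extremes. They show that the sign of the bias depends on who is lost, which the protocol cannot tell us.

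**The case against.** The strongest defence reads the sections together. The protocol adopts RECIST and the appendix gives early deaths and not-assessable patients a category, so they have an endpoint and the condition in 7.4 bites mainly on missing SUVs. That reading is possible, but 7.4 does not state it and the protocol never defines those categories. The appendix passage is also a generic reference written for the response rate, so it reaches the progression split in the ROC only by extension. The charge is therefore an unresolved conflict in the definition of the primary set, which is more than a detail left to an analysis plan.

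On withdrawals, sections 3.4 and 5.7 both call for documentation after termination. That stands: the off-study wording in 6.3 clashes with them, but no loss of data is demonstrated.

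A reader might go further in three ways that the documents do not support:
- **All early progressers are removed.** Progression documented before week 7 is an available endpoint, and the appendix asks for every effort to document progression after discontinuation.
- **Power collapses towards 53%.** That assumes every loss is a progresser from one tail of the PET distribution; the opposite tail raises the AUC and power.
- **Every patient without a CT should count as a progresser in the primary ROC.** For toxicity withdrawals, other deaths and unknowns this puts error into the reference standard. In simulation, mislabelling 2 to 3 of 16 true non-progressers lowers the AUC to 0.72 to 0.73 and power to about 64 to 75%.

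**Conclusion.** The point holds as a defect in the definition of the primary set: 7.4 conditions on endpoint availability, the label says otherwise, and the adopted RECIST appendix treats the same patients differently. Those at risk are early disease deaths, deterioration without imaging and withdrawals.

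The sample size has no allowance for loss. The power cost is moderate: from 80% to about 73 to 77% for 10 to 15% loss. This rests on an assumed loss rate. The 13% anchor comes from another cohort, and the protocol does not say why those seven patients were not evaluable. Bias in the AUC is possible in either direction and its size cannot be fixed from the document.

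In an exploratory single-arm phase II trial this should be fixed, and before outcomes are known, but it does not invalidate the design.

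**What to change.** 1. **Section 7.4.** Replace the bracketed condition with: all patients with an evaluable PET between days 7 and 14 enter the primary analysis; death from disease, or documented clinical or radiological progression, before the week-7 CT counts as progression; patients without a week-7 outcome for other reasons (toxicity, other death, unknown) are reported, with one sensitivity analysis classing them as progressers as in Appendix 12.3 and one excluding them.
2. **Safety.** Define the safety population separately as all treated patients.
3. **Sections 6.3 and 3.4.** Reconcile the off-study and withdrawal wording with the required follow-up, so that the already scheduled week-7 CT is still obtained where possible. No treatment-stopping rule changes.
4. **Section 7.3.** State that 80% power applies to 40 evaluable patients and give the power at the expected loss.

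The cost is protocol wording and keeping a CT that is already scheduled. A few patients will be classed as progressers without CT confirmation, and the stated power will be somewhat lower. Patients lost before the early PET remain outside the ROC and should be counted and reported.

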## **8 DOCUMENTATION AND MONITORING**

All data collected are documented on standardized case report forms (CRF) by the treating physician or other persons given the responsibility for documentation.

A multilevel plan for data validation has been drawn up. In case of missing or inconsistent data, a data manager will contact the treating physician or person responsible for documentation in the department by telephone or in writing (queries).

### **8.1 Direct access to source data**

A regulatory authority may wish to conduct an inspection (during the trial or even after its completion). If an inspection is requested by a regulatory authority, the investigator must inform the trial coordination center immediately that this request has been made. The investigator will permit trial-related monitoring, audits, reviews by the independent ethics committee, and regulatory inspections, providing direct access to source data and documents.

### **8.2 Quality control and assurance**

Each investigator is responsible at his site that the trial is performed in accordance with GCP, AMG and the protocol. He ensures that data is collected as stated in the protocol and

documented correctly in the responding CRF. Monitors will assist investigators in reviewing the complete, legible, clearly arranged and recallable data. All data is examined by the monitors.

### **8.3 Monitoring**

In order to guarantee a high quality of the trial and data retrieval, all participating centers will be visited on a regular base on site by monitors.

Data protection rights will be respected. Patient files will be analyzed on a random base to control original data and to verify accurate data registration and management. The presence of a written informed consent form and the correct interpretation of inclusion and exclusion criteria will be controlled. The monitor will also have regular contact by phone and/or e-mail with all participating centers.

The investigator agrees that the trial center will be visited on a regular base on site by the monitor and will support the monitor in his/her activities.

Purpose of this visits are:

- Evaluation of the trial progression
- Adherence to the trial protocol
- Discussion of problems related to trial problems (adverse events)
- Check of the CRFs concerning accuracy and completeness
- Validation of the CRFs compared to the source data
- Control of the administration of the trial medication

The monitor writes a monitoring-report about each visit. In this monitoring report will be documented the trial progress and all appearing problems.

### **Data handling and record keeping**

#### **Documentation**

All protocol required procedures along with information necessary to report the observations and tests described in this protocol will be recorded in the Case report forms (CRFs). CRFs must be completed and given to the trial coordination center in a timely and accurate manner by site personnel.

CT scans must be reported in summary in the CRF. The original reports, traces and films must be retained by the investigator for future reference.

The investigator must review all pages within the CRF for accuracy and consistency with the protocol, and sign and date the CRF sign-off page(s) upon completion.

Corrections to data on the CRFs must be made by lining out the incorrect data with a single line and writing the correct data near to those crossed out. Correction fluid is not to be used

## ETHICAL MATTERS

to cover errors. Each correction must be initialed and dated by the person making the correction.

The patient consent forms designated for the clinical investigator are also to be kept in the trial documentation. All the information on which the entries in the CRF are based must be available in the patient files e. g. results of laboratory investigations.

After prior agreement, a check of the consistency of data between the patient files, raw data and CRF as well as with other documents related to the trial will be conducted by the responsible authorities and/or by monitors (inspection/audit/monitoring).

The clinical investigator is responsible for the identity of the data in the patient file and the correct entry of the data into the CRF.

### Data management

All incoming CRF and DCF will be registered by the data management. All registration forms will be checked for completeness, plausibility, and correctness. Missing, questionable, or additional information will be requested on a regular base by the data management. The data management will remind for missing documentation regularly.

Data will be entered into an Oracle database using MACRO as the data entry application. During entry data will be checked by constraints and triggers.

The database will be checked for faults and validated by the database programmer. Thereafter the database will approve the database for data entry. Complete and incremental data backup will be performed regularly.

All CRFs and other essential trial documents will be archived for at least 15 years. Patients ID-lists and medical records will be kept separately at the individual trial sites.

### Record keeping

A copy of the final completed CRFs is retained by the investigator, who must ensure that it is stored with other trial documents, such as the protocol, the investigator's brochure and any protocol amendments, in a secure place.

Case records and raw data are to be retained for at least 15 years following the end of the trial. The investigator will ensure that a correct assignment of the CRFs to the corresponding patient files and raw data is possible at any time. A separate patient identification list must be recorded by the investigator. Patients ID-lists and medical records will be kept separately at the individual trial sites by the investigator.

## 9 ETHICAL MATTERS

The trial is performed according to the declaration of Helsinki (Helsinki, 2000) and the principles of the ICH guidelines on Good Clinical Practice (Spira and Ettinger, 2004). The ICH guidelines have been adapted to the conditions applying to quality assurance protocols in clinical trials groups.

## ORGANIZATION

The trial coordinators have obtained a vote of approval from the local responsible ethical committee - (Ethikkommission der Universität zu Köln) of the responsible authorities (BfArM and BFS) according to the German drug regulations (Arzneimittelgesetz, 2004).

For PET diagnostics, the trial coordinators will obtain the approval of the German Authority for Radiation Safety (Bundesamt für Strahlenschutz). As synthesis and application of FLT and FDG is performed within the trial center, §4a.3 of the AMG is applicable.

Other radiation burdens (radiotherapy, X-rays) lie within the range of usual medical care and approval is therefore, under present legislation, not required.

The trial coordinators will obtain approval from the responsible ethical committee, according to the German drug regulations, whenever the trial protocol is amended such as to require renewed assessment of risk to patients (e.g. changes to dose or to duration of treatment, or the occurrence of serious adverse events).

Roche will fulfill reporting requirements to authorities and ethics committees. SUSARs will be distributed to ethics committees and centers by Roche.

